### Outcome measures

#### Primary outcome

The primary outcome of the PREP trial is the incidence of PPCs within the first 14 post-operative days. PPCs is defined with the Melbourne Group Scale (MGS) diagnostic scoring tool, which is reliable and valid following thoracic surgery with high inter-rater reliability [35–37]. A PPC will be diagnosed when the following four or more factors are identified: 1) new abnormal breath sounds different to pre-operative; 2) chest X-ray findings of atelectasis or consolidation; 3) raised white cell count (WCC) (> 11 × 10^9^/L); 4) temperature > 38 °C; 5) purulent sputum differing from preoperative status; 6) signs of infection on sputum culture; 7) pulse oximetry oxygen saturation (SpO_2_) < 90% without oxygen therapy; and 8) pneumonia diagnosed based on physician’s experience [38]. When a positive diagnosis of a PPC is confirmed, the patient will then receive specific respiratory interventions provided by the doctors from Department of Respiration.

Patients will be assessed for PPCs at each prospective day by a blinded assessor. Medical documents including radiologist reports and laboratory sheets will be reviewed as references. A log-sheet will be provided to the patients on their discharge day to record any self-identified respiratory symptoms in the following consecutive days till Day 14. These data may sever as references for diagnosis of PPCs during their stay at home. The patients will be requested to submit the log-sheets to the assessor for recording on their follow up days. They will be suggested to readmitted to the hospital in case of any severe symptom occurs.

#### Secondary outcomes

Secondary outcomes are listed as follows:
Cardiopulmonary complications, other than those defined in the MGS, include atelectasis, respiratory failure, pleural effusion, pneumothorax, pulmonary embolism, arrhythmia, heart failure and thoracic hemorrhage;Other complications include hypovolemia, wound lacerations, wound hemorrhage, wound dehiscence, wound infection, urinary tract infection, sepsis, delirium, reintubation and fall;Pulmonary function will be reflected by forced vital capacity (FVC), forced expiratory volume in the first second (FEV_1_), ratio between FEV_1_ and FVC (FEV_1_/FVC), peak expiratory flow (PEF) [39, 40];Cardiopulmonary endurance will be reflected by the 6-min walking test (6MWT) [27];Muscle strength will be reflected by maximum grip strength as measured on the dominant hand using a calibrated hand dynamometer [41];Activity level will be reflected by self-reported metabolic equivalents (METs) [42];Health-related quality of life (HRQoL) will be evaluated with SF-12 [43];Time in day for the pre- and post- operative application of antibiotics;Pre- and post-operative hospital LOS and total hospital LOS.

### Data collection

Data in terms of PPC defined in the MGS, cardiopulmonary complications (i.e. coronary heart disease, hypertension, COPD), other complications (i.e. diabetes), pulmonary function, cardiopulmonary endurance, muscle strength, activity level and HRQoL will be selectively collected on the admission day (baseline), on the discharge day (second follow-up), 2 weeks post operation (third follow-up) and 12 weeks post operation (forth follow-up). Scheduled data collection at each time point is presented in Table 2.

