**Table 2 Tab2:**
[figure not shown]
Scheduled events and timeline of PREP trial

*PPCs* post-operative pulmonary complications, *HRQoL* health-related quality of life, *LOS* length of stay

Apart from the above variables, demographics and clinical characteristics, collected directly from the patients or the medical documents, are as follows: center of recruitment, phone number, age, gender, height in centimeter, weight in kilogram, smoking history (never smoked, former smoker or current smoker), smoking index in average pack years, pre-operative comorbidities (cardiac disease, diabetes mellitus, hypertension, respiratory infection or others), pre- and post-operative hospital LOS and total hospital LOS.

Surgery-related variables will be collected from the anesthetic record, operation report and medical document: type of lung cancer according to the intra- or post-operative pathological examination, tumor location (left lower lobe, left upper lobe, right lower lobe, right middle lobe, right upper lobe) [44], surgical type (lobectomy, segmentectomy, pneumonectomy or sleeve) [36], length in minute of surgery, immediate post-operative location (surgical ward or ICU), post-operative antibiotic delivery (time in day and type of antibiotic delivered and reason to upgrade or downgrade), post-operative pain management (oral, intramuscular injection, intravenous administration or epidural administration), and postoperative daily drainage in milliliter.

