### Statistical methods

Backward stepwise regression will be applied to select adjustment covariates from covariates which may have impact on the prognostic strength and effect sizes between groups. These covariates include: age, gender, BMI, smoking history, smoking index, pre-operative comorbidities and physical status, pre-operative hospital LOS, application of prophylactic antibiotics, surgical type, tumor location, length in time of operation, ICU admission immediately following the surgery, mode of post-operative analgesia, type of lung cancer according to the intra- or post-operative pathological examination, time in day and type of post-operative antibiotic delivery, post-operative analgesia management, and postoperative daily drainage [46, 47].

For all outcomes we estimated differences in effect size between groups on an intention-to-treat basis. Multivariate robust random or mixed effects Poisson regression will be applied to estimate primary outcome efficacy and binomial secondary outcomes (cardiopulmonary complications and other complications). The time effect of day the PPC diagnosed between groups will be estimated with Cox proportional hazards regression with or without adjustment for covariates. Secondary outcomes with normal and abnormal distributions, including cardiopulmonary endurance, muscle strength, activity level, HRQoL, time in day of the application of antibiotics, pre- and post-operative hospital LOS and total hospital LOS, will be estimated for group differences with mixed effects ordered logistic regression and mixed effects linear regression.

Exploratory post hoc sensitivity adjusted analyses will be performed to determine the effect of specific covariates (discrepancy in experience grade of treating physiotherapist, hospital level, surgical category, tumor location, preoperative respiratory complication risk score, age and gender) across all primary and major secondary outcomes [48].

All analyses will be performed using Stata version 16 or later (StataCorp, College Station, TX, USA).

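### Data collection fills the two secondary complication outcomes with chronic diseases that conflict with the acute events in Secondary outcomes, and atelectasis is not separated from the MGS

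*Protocol article*

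**What the plan says.** Four places in the protocol article bear on the two complication outcomes.

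- **Secondary outcomes** lists acute events. The first outcome reads "Cardiopulmonary complications, other than those defined in the MGS, include atelectasis, respiratory failure, pleural effusion, pneumothorax, pulmonary embolism, arrhythmia, heart failure and thoracic hemorrhage". The second reads "Other complications include hypovolemia, wound lacerations, wound hemorrhage, wound dehiscence, wound infection, urinary tract infection, sepsis, delirium, reintubation and fall".
- **Data collection** uses the same two labels but fills them differently: "cardiopulmonary complications (i.e. coronary heart disease, hypertension, COPD), other complications (i.e. diabetes". These data, with the other outcomes, "will be selectively collected on the admission day (baseline), on the discharge day (second follow-up), 2 weeks post operation (third follow-up", and again at 12 weeks. The section refers to Table 2 for the schedule; that table is not available to this review.
- **Data collection, below Table 2**, names a further set of variables, introduced as additional to those already named. It includes "pre-operative comorbidities (cardiac disease, diabetes mellitus, hypertension, respiratory infection or others".
- **Statistical methods** analyses the two labels as "binomial secondary outcomes (cardiopulmonary complications and other complications", and also lists pre-operative comorbidities among the candidate adjustment covariates.

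On atelectasis, **Primary outcome** has "chest X-ray findings of atelectasis or consolidation" as the second of eight MGS factors, and a PPC needs at least four of the eight. Secondary outcomes puts atelectasis first in a list described as lying outside the MGS.

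**The concern.** An outcome label should have one content. Here the outcome section describes acute events after surgery, while the data-collection section describes long-standing disease under the same names. If a site or the coordinating center followed the second description, a patient admitted with hypertension or diabetes would be an event in either arm whatever the treatment did. Such events add the same expected background to both arms and pull the estimate towards no effect. The same condition could also enter the model as an adjustment covariate for an outcome of which it is part.

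The atelectasis wording raises a smaller question: whether a patient who meets the primary outcome partly because of atelectasis also counts in a secondary outcome that is presented as separate from it.

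**Working it through.** **Chronic disease under an outcome label.** The plan has no figure to reproduce here, so the check is mainly one of text.

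| Label | Secondary outcomes | Data collection | Comorbidity list |
|---|---|---|---|
| Cardiopulmonary complications | Eight acute events, atelectasis to thoracic hemorrhage | Coronary heart disease, hypertension, COPD | Cardiac disease and hypertension named; COPD fits only the residual category |
| Other complications | Ten acute events, hypovolemia to fall | Diabetes | Diabetes mellitus named |

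None of the four diseases in the third column appears in the second. Three features of the text suggest that the Data collection sentence is about outcomes:

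1. It runs through PPC, the two complication labels, pulmonary function, endurance, strength, activity level and HRQoL in the same order as the outcome sections.
2. It covers discharge, 2 weeks and 12 weeks as well as admission.
3. Comorbidities are introduced afterwards as something additional.

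**What literal use would do (illustration only).** Every input is an assumption for these outcomes:

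- Acute risk e of 20% in control and 10% in intervention. These are borrowed from the Sample size calculation section, which states them for PPCs, not for these outcomes.
- 250 analysed per arm, half of the target of 500, with no loss.
- A chronic disease of prevalence q, equal in both arms, independent of acute events and always counted as an event.
- An unadjusted two-sided test at 0.05.

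Recorded risk = 1 − (1 − e)(1 − q). The risk difference is therefore the true one multiplied by (1 − q). For q = 0.20:

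- control: 1 − 0.80 × 0.80 = 0.36
- intervention: 1 − 0.90 × 0.80 = 0.28
- difference: 0.08 = 0.10 × 0.80; ratio: 0.28 / 0.36 = 0.78

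Power = Φ{[d − 1.96 √(2p̄(1 − p̄)/n)] / √([p₁(1 − p₁) + p₂(1 − p₂)]/n)}, where d is the risk difference and p̄ the mean of the two risks. For q = 0.20, p̄ = 0.32:

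- 1.96 × √(2 × 0.32 × 0.68 / 250) = 1.96 × 0.04172 = 0.0818
- √((0.2304 + 0.2016)/250) = 0.0416
- Φ((0.08 − 0.0818)/0.0416) = Φ(−0.04) = 0.48

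| Assumed q | Control | Intervention | Risk ratio | Power |
|---|---|---|---|---|
| 0 | 20% | 10% | 0.50 | 0.88 |
| 0.10 | 28% | 19% | 0.68 | 0.66 |
| 0.20 | 36% | 28% | 0.78 | 0.48 |
| 0.30 | 44% | 37% | 0.84 | 0.36 |
| 0.40 | 52% | 46% | 0.88 | 0.27 |
| 0.60 | 68% | 64% | 0.94 | 0.16 |

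**Atelectasis.** There are three cases under the text as written:

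1. Atelectasis with fewer than three other MGS factors: not a PPC. It counts only in the secondary outcome.
2. Atelectasis with three or more other factors: a PPC. Because atelectasis is also in the secondary list, the patient can count there too.
3. A PPC reached without atelectasis: no overlap from this source.

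Only the second case conflicts with describing the secondary list as separate from the MGS.

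**The case against.** The strongest reply is that the Data collection sentence is a slip of the pen, with complications written for comorbidities. The outcomes are defined under their own heading. Taken literally, diabetes would be the whole of the second outcome, which is implausible beside a list of ten acute events. The article's English is loose elsewhere, the sentence includes the admission visit, and it says that items are collected selectively. Sites work from trial-specific case report forms and trained procedures, and neither these nor Table 2 can be seen here.

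Much of this stands. A reader might infer that the abbreviation i.e. turns the chronic diseases into the definition of the outcomes, or that sites will certainly count them. The documents do not support that: the sentence is about collection, and nothing shows how the forms or the analysis treat these diseases. The slip remains a guess, however. The separate comorbidity list and the follow-up visits count against it, and a slip in a collection instruction used at six centers still needs correcting.

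A reader might also take the power table as a loss that the trial will suffer. It is not. The plan states no rates and claims no power for these outcomes, and comorbidities are candidate covariates, which the unadjusted illustration leaves out.

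On atelectasis, a reader might infer that every case counts twice and that it should be struck from the secondary list. That overlooks the threshold. Isolated atelectasis is not an MGS-defined PPC, and the phrase about lying outside the MGS can fairly mean events that fall short of one. Striking it would remove sub-threshold atelectasis from every outcome. What remains is that the article does not say how atelectasis counts once the threshold is met.

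**Conclusion.** The contradiction is in the text and holds: one pair of outcome labels has two incompatible contents, and one of them overlaps with the baseline comorbidities. Whether it affects the data is not known. If the Data collection wording were followed, the risk difference would shrink by the factor (1 − q) under equal and independent prevalence q. The risk ratios of 0.68 to 0.94 in the table rest wholly on assumed rates.

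The atelectasis point is an unclear boundary, limited to patients with atelectasis who also reach four MGS factors. The primary outcome definition and the sample size are untouched by either point. This is an inconsistency to correct in the secondary complication outcomes, not a threat to the main result.

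**What to change.** 1. In Data collection, replace the two bracketed disease lists with a reference to the lists in Secondary outcomes.
2. State that only events with onset after surgery count towards the two complication outcomes.
3. Record chronic disease once, as baseline comorbidity, and name COPD there.
4. Keep atelectasis in the secondary outcome, but state that it counts there only when the patient does not meet the four-factor MGS threshold. Alternatively, state openly that the primary and secondary outcomes overlap.
5. Enrollment began on 1 August 2019, so check the case report form labels and the forms already completed for chronic disease entered as a complication.

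The cost is a few sentences, possibly a form label, and a check of existing forms. No change to the sample size or the primary analysis is needed.

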**Table 2 Tab2:**
[figure not shown]
Scheduled events and timeline of PREP trial

*PPCs* post-operative pulmonary complications, *HRQoL* health-related quality of life, *LOS* length of stay

Apart from the above variables, demographics and clinical characteristics, collected directly from the patients or the medical documents, are as follows: center of recruitment, phone number, age, gender, height in centimeter, weight in kilogram, smoking history (never smoked, former smoker or current smoker), smoking index in average pack years, pre-operative comorbidities (cardiac disease, diabetes mellitus, hypertension, respiratory infection or others), pre- and post-operative hospital LOS and total hospital LOS.

Surgery-related variables will be collected from the anesthetic record, operation report and medical document: type of lung cancer according to the intra- or post-operative pathological examination, tumor location (left lower lobe, left upper lobe, right lower lobe, right middle lobe, right upper lobe) [44], surgical type (lobectomy, segmentectomy, pneumonectomy or sleeve) [36], length in minute of surgery, immediate post-operative location (surgical ward or ICU), post-operative antibiotic delivery (time in day and type of antibiotic delivered and reason to upgrade or downgrade), post-operative pain management (oral, intramuscular injection, intravenous administration or epidural administration), and postoperative daily drainage in milliliter.

### Sample size calculation

It has been reported that the absolute risk reduction in PPCs was of 20% by previous trials of preoperative education [45], and a post-operative PPC incidence of 32% was identified in patients with undergoing minimally invasive lung cancer surgery [2]. For the purposes of this trial, conservative goals (minimum 10% absolute risk reduction from a 20% baseline PPC risk) were set. A sample of 305 patients would have 80% power to detect a significant difference between groups (*p* = 0.05, two sided) with an 15% inflation to account for dropouts, non-compliance, and uncertainty of baseline risk, providing a final sample size of 500.

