Enhanced Recovery After Surgery (ERAS) practices improve the opportunity for rapid, uncomplicated recovery after surgery with both short- and long-term benefits for patients [18]. Data suggest that complication rates can be reduced by 10–50% or more with supporting units to adopt evidence-based EARS care [19–22]. Further data also showed that not only were overall complications reduced, but the most severe complications, which resulted in decreased rates of reoperation or admission to the intensive care unit (ICU) as mortality improved [20, 23]. Recently, ERAS principles have been applied across most surgical specialties. After the ERAS Society was formed in 2010, the Society published a series of guidelines and recommendations on colonic resection, rectal resection and pancreaticoduodenectomy in 2012, cystectomy and gastric resection in 2015, bariatric surgery, liver resection, and head and neck cancer surgery in 2016, breast reconstruction in 2017 [18]. Nonetheless, the ERAS guideline for thoracic surgery is still under production, revealing that there is a paucity of quality resear on adopting these principles in this field. To date, no multicenter randomized controlled trials (RCTs) support the provision of pulmonary rehabilitation based ERAS program (PREP) on reducing PPCs and shortening recovery time, which translate to a substantial improvement of quality of life (QoL) following the ERAS principle. Considering the high incidence of PPCs following lung cancer surgery, ongoing innovation must move from guessing to knowing the outcomes though adequately powered research. Therefore, a well-designed, multicenter RCT is needed to determine the clinical effects of pulmonary rehabilitation based ERAS program on reducing incidence of PPCs following lung cancer surgery. The results of the current trial may fill the blank of applying ERAS program in this field and may contribute to the construction of ERAS guideline on lung cancer surgery.

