### Recruitment, randomization and allocation

Eligible patients potentially undergoing lung cancer surgery at the participating centers will be assessed by a multi-disciplinary team consisting of a registered nurse, anesthetist, and surgeon from the admitting surgical team one to 2 weeks prior to their operation. Face-to-face pre-operative education in terms of the surgical process, pain management, postoperative drips and drains, and expected recovery process will be delivered.

Six sets of allocation sequence is determined by a web-based computer generated (http://www.randomizer.org/) random number table (Odd = intervention, Even = control). These tables are then sealed in six sets of 150 sequentially numbered (1 to 150) opaque envelopes, each containing an allocation card, prepared by a medical staff masked to the trial [31].

Eligible patients will be provided with a sheet including trial information about the randomization process, the discrepant rehabilitation plans, the surgical process, pain management, postoperative drips and drains, and expected recovery process. Those agreeing will sign a consent form as required by the ethics committee and in accordance with the Declaration of Helsinki.

Once informed consent form has been signed, patients will be allocated to one of the two experimental groups, by opening the sequentially numbered opaque envelopes, to receive 1) a pre-operative assessment and an information booklet (control) or 2) a pre-operative assessment, an information booklet, plus an additional education, a 30-min pulmonary rehabilitation training session and the post-operative pulmonary rehabilitation program (intervention). A trial participation sticker containing patient details will be attached on the opened envelope which will be filed securely with the informed consent form. Figure 1 demonstrates the overview of the recruitment, randomization and allocation based on the CONSORT principle.

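### On its stated inputs, 305 patients give about 69% power rather than 80%, and a 15% inflation of 305 does not lead to 500

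*Protocol article*

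**What the plan says.** All the inputs and both results stand in one paragraph of the protocol article, under Sample size calculation.

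- **Effect:** "conservative goals (minimum 10% absolute risk reduction from a 20% baseline PPC risk) were set", that is, 20% against 10%.
- **Error rate:** "0.05, two sided".
- **Number before inflation:** "A sample of 305 patients would have 80% power to detect a significant difference between groups".
- **Inflation and total:** "with an 15% inflation to account for dropouts, non-compliance, and uncertainty of baseline risk, providing a final sample size of 500".

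The Abstract and Table 1 also give 500 as the total. No allocation ratio is stated. I take it as 1:1 from the rule under Recruitment, randomization and allocation: "Odd = intervention, Even = control". The article does not name the sample-size formula and does not explain the step from 305 to 500.

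**The concern.** The paragraph makes two numerical claims that can be checked from what it prints, so this is not a matter of detail left to a fuller protocol or an analysis plan. The first is that 305 patients suffice for 80% power at 20% against 10%. The second is that 305 plus 15% is 500. A quick check contradicts both.

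This paragraph is the only justification given for the target of 500. It is also the only place that tells a reader how many analysable patients the primary comparison needs. As printed, it puts that number at 305, which is 93 below the 398 that the inputs require.

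**Working it through.** **Inputs.** p1 = 0.20, p2 = 0.10, two-sided α = 0.05 and power 80% (all from Sample size calculation); 1:1 allocation (inferred, as above). So z(0.975) = 1.960, z(0.80) = 0.8416, p̄ = 0.15 and d = 0.10.

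**1. Can 305 be reproduced?** Pooled two-proportion formula, per arm:

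n = [1.960·√(2p̄(1−p̄)) + 0.8416·√(p1(1−p1) + p2(1−p2))]² / d²

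- √(2 × 0.15 × 0.85) = √0.255 = 0.5050
- √(0.16 + 0.09) = 0.5000
- n = (0.9897 + 0.4208)² / 0.01 = 198.96, so 199 per arm and **398 in total**

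With continuity correction: n' = (198.96/4) × [1 + √(1 + 4/(198.96 × 0.10))]² = 218.5, so 219 per arm and **438 in total**.

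Other two-sided methods at 80% power:

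| Method | Total |
|---|---|
| Arcsine | 390 |
| Unpooled variance | 394 |
| Pooled variance | 398 |
| Fisher exact | about 426 to 428 |
| Continuity-corrected | 438 |

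None is near 305.

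**2. What power does a given total N have?** Power = Φ[(d·√(N/2) − 0.9897) / 0.5000].

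| Total analysed | Calculation | Power |
|---|---|---|
| 305 | (1.2349 − 0.9897)/0.5 = 0.490 | 68.8% |
| 398 | (1.4107 − 0.9897)/0.5 = 0.842 | 80.0% |
| 425 | (1.4577 − 0.9897)/0.5 = 0.936 | 82.5% |
| 500 | (1.5811 − 0.9897)/0.5 = 1.183 | 88.2% |
| 610 | (1.7464 − 0.9897)/0.5 = 1.513 | 93.5% |

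**3. Does 15% lead from 305 to 500?**

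- 305 × 1.15 = 351
- 305 / 0.85 = 359
- 500 / 305 = 1.64, a 64% inflation; equivalently, 1 − 305/500 = 39% loss allowed

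**4. Is 305 a per-arm number?** Then the total is 610 before inflation, and 702 (×1.15) or 718 (/0.85) after it. All three exceed 500, and 610 gives 93.5% power, not 80%.

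**5. What does support 500?** 398 × 1.15 = 458 and 398/0.85 = 469, both under 500. The continuity-corrected 438 × 1.15 = 504, close to 500, and 438/0.85 = 516. Working back, 500 × 0.85 = 425 analysable patients, with 82.5% power by the pooled formula.

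**6. Where might 305 come from?** A one-sided 0.05 test of 20% against 10% needs 314 in total by the pooled formula (310 unpooled, 308 arcsine), and 305 then gives 79.1% power. A two-sided test of 25% against 12.5% needs 152 per arm, 304 in total. Both come close, but the first contradicts the stated two-sided test and the second contradicts the stated 20% baseline. Either origin is a guess.

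These figures ignore clustering by centre and covariate adjustment, for which the article gives no values.

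**The case against.** The strongest reply is that the operative number is 500, given consistently in the Abstract, in Table 1 and in the sample-size section, and that 500 is enough for the declared effect. No section makes 305 a recruitment, stopping or monitoring threshold, and Data monitoring does not mention it. That stands, and it limits the consequence to a wrong statement and a broken derivation.

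It does not rescue the statement. The inputs and results are printed together and disagree.

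A reader might infer more, and the documents do not support these stronger readings:

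- **That the trial is underpowered.** For 20% against 10% it is not: power is 82.5% after 15% loss.
- **That calling the goals conservative is wrong.** For a fixed 10-point difference a 20% baseline is indeed easier than 32%. But the section first cites a 20-point reduction and a 32% incidence, and the planned effect is smaller than that on both scales: 10 points against 20 absolute, and 10/20 = 50% against 20/32 = 62.5% relative.
- **That a 50% relative reduction sits at the ceiling of the cited evidence.** The Background says "complication rates can be reduced by 10–50% or more", so 50% is not a ceiling.
- **That the allowance for uncertain baseline risk fails at 32%.** This depends on the effect scale. With 425 analysable patients, 32% against 22% has 64% power, but 32% against 16% has 97%. The article does not say which effect would hold at another baseline.
- **That non-compliance takes power below 80%.** Such a figure needs an assumed share of the exercise arm with no benefit, and the article gives none.

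**Conclusion.** The point holds for two statements. First, 305 patients in total give 68.8% power on the stated inputs, where the article claims 80%; the required total is 398, or 438 with continuity correction. Second, a 15% inflation takes 305 to 351 or 359, and the printed 500 is a 64% increase. Reading 305 as per arm makes the mismatch worse.

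The conclusion rests on 1:1 allocation, which is inferred, and on an unadjusted comparison of two proportions. It does not depend on the choice among the usual two-sided formulas, since all need between 390 and 438.

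The power statement for the primary outcome is incorrect and cannot be reproduced, so it needs correcting. The target of 500 remains adequate for the declared effect, and nothing here calls for more patients.

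**What to change.** Keep 500. Replace 305 with the number that follows from the stated inputs, name the formula, and show each step to the total. Suggested wording:

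*By the pooled two-proportion formula, 398 evaluable patients (199 per arm, 1:1) give 80% power for 20% versus 10%, two-sided 0.05. Allowing 15% loss requires 469. Recruiting 500 leaves 425 evaluable and 82.5% power.*

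If 305 came from other inputs, such as a one-sided test or another baseline rate, the sponsor should state those inputs and reconcile 305, 15% and 500, rather than adopt this wording.

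Power at other control rates is optional. If it is added, the text must say whether the absolute or the relative effect is held fixed.

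The cost is wording only: no extra patients, and no change to design or analysis.
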